# Abbreviations

| Abbreviation | Full names |
| --- | --- |
| rAAV | Recombinant adeno-associated virus |
| vg | Viral genome |
| AE | Adverse events |
| APTT | Activated partial thromboplastin time |
| BCVA | Best-corrected visual acuity |
| Cr | Creatinine |
| CNV | Choroidal neovascularisation |
| eCRF | Electronic case report form |
| ELISA | Enzyme-linked immunosorbent assay |
| ETDRS Chart | Early Treatment of Diabetic Retinopathy Study |
| FAS | Full Analysis Set |
| GCP | Good Clinical Practice |
| HbsAg | Hepatitis B surface antigen |
| HCV-Ab | Hepatitis C virus antibody |
| HIV-Ab | Human immunodeficiency virus antibody |
| IOP | Intraocular pressure |
| NMPA | National Medical Products Administration |
| PT | Prothrombin time |
| SAE | Serious adverse events |
| SS | Safety Set |
| TBIL | Total bilirubin |
| TC | Total cholesterol |
| TG | Triglycerides |
| OCT | Optical coherence tomography |

# Protocol Synopsis

| **Sponsor:** Beijing Tongren Hospital, Capital Medical University |
| --- |
| **Cooperative Unit:** Chigenovo Co., Ltd. |
| **Study Phase:** Investigator-initiated trial |
| **Study Title:** A Safety Study of a Single Subretinal Injection of rAAV2/8-hCYP4V2 Gene Replacement Therapy in Patients with Bietti's Crystalline Dystrophy (BCD) |
| **Indication: Bietti's crystalline dystrophy (BCD)** |
| **Study Objectives:**  Primary objective: To evaluate the safety of a single subretinal injection of rAAV2/8-hCYP4V2 in patients with Bietti's crystalline dystrophy (BCD).  Secondary objective: To preliminarily explore the clinical efficacy of rAAV2/8-hCYP4V2 gene replacement therapy. |
| **Investigational Drug:** rAAV2/8-hCYP4V2 Ophthalmic Injection, provided by Chigenovo Co., Ltd. and manufactured by OBiO Technology (Shanghai) Corp., Ltd. (The internal code is ZVS101e in Chigenovo Co., Ltd., and C035 Injection in OBiO Technology (Shanghai) Corp., Ltd.)  **Strength:** 2×10^12^ vg/mL, 0.2 mL/vial, diluted to 5×10^8^ vg/uL before use  **Injection Volume:** 150 uL  **Dose of Administration:** 7.5×10^10^ vg  **Method of administration:** Subretinal injection |
| **Rationale for Dose Design**  The investigational drug rAAV2/8-hCYP4V2 Ophthalmic Injection is a gene replacement therapy drug. In preliminary safety clinical study (ClinicalTrials No.: NCT04722107), enrollment, administration, and 3-month safety and efficacy observation have been completed in 3 subjects. During the observation period, no drug- or treatment-related serious adverse reactions occurred in any of the 3 subjects; meanwhile, 2 of the subjects showed significant improvements in visual acuity and Multi-Luminance Mobility Test (MLMT) score. It can be seen that the clinical dose of 5×10^8^ vg/uL has good safety and certain efficacy. Preclinical pharmacodynamic experiment has preliminarily demonstrated that 1 uL of the following concentrations of rAAV2/8-hCYP4V2 were injected into the subretinal space of CYP4V2 knockout mice: CYP4V2 protein was expressed in 1×10^8^, 5×10^8^, 1×10^9^, 3×10^9^, 6×10^9^ and 1×10^10^ (unit: vg/uL), and the 6-month in vivo observation at following three doses of 3×10^9^ vg, 6×10^9^ vg and 1×10^10^ vg showed that 3×10^9^ vg had a significant therapeutic effect without obvious toxicities, and 6×10^9^ vg and 1×10^10^ vg had efficacy in the early stage, but obvious retinal toxicity in the later stage.  Referring to Luxturna (produced by Spark, intended for LCA patients carrying RPE65 gene mutation), the only gene replacement therapy marketed in the field of inherited retinal degeneration, the dose escalation concentration of Luxturna is designed as: 1×10^8^ (150 uL), 3.2×10^8^ (150 uL) and 5×10^8^ (300 uL) (unit: vg/uL). The dose escalation study results showed that all of the above three concentrations had therapeutic effect without obvious toxicities. The recommended Phase 3 clinical trial concentration of Luxturna was 5×10^8^ vg/uL (300 uL), which was the maximum concentration tested in vivo.  Referring to the clinical study data of RPGR gene replacement therapy drug published in Nature Medicine in February 2020, the dose escalation concentrations were designed as six doses: 5×10^7^ (40-100 uL), 1×10^8^ (40-100 uL), 5×10^8^ (30-100 uL), 1×10^9^ (60-100 uL), 2.5×10^9^ (50-150 uL) and 5×10^9^ (30-80 uL) (unit: vg/uL). The results showed that 5×10^7^ vg/uL and 1×10^8^ vg/uL groups had no significant improvement in visual function, 5×10^8^ vg/uL group had significant improvement, and 7 of 9 subjects in the three high-dose groups (1×10^11^ vg, 2.5×10^11^ vg and 5×10^11^ vg) showed mild inflammatory reaction, which could be effectively managed after hormone therapy.  Based on the preclinical results of the investigational drug and comparison with similar drugs, and referring to the dose design for Phase 1 dose escalation study and recommended clinical dose of the similar marketed drug Luxturna, the concentration gradient selected in this project is: 1×10^8^ vg/uL, 5×10^8^ vg/uL, 1×10^9^ vg/uL and 3×10^9^ vg/uL, and the injection dose is 150 uL. In this preliminary experiment, the concentration selected was 5×10^8^ vg/uL, 150 uL, so the injection dose was 7.5×10^10^ vg. |
| **Study Design**  This is a single-center, open-label, single-arm and single-dose study and aimed to evaluate the safety and preliminary efficacy of the investigational drug in patient with BCD.  **Selection Criteria for Target Eye**  The target eye must meet the following requirements:  1) Best-corrected visual acuity is counting finger to 0.3 (equivalent to Snellen visual counting finger to 20/63); able to perform visual examination and retinal function test; photoreceptor layer, that is, the outer nuclear layer can be observed in macular area under standard optical coherence tomography (OCT);  2) The eye with poorer visual acuity in both eyes of the candidate subject is the target eye. Note: For all subjects, only one eye is designated as the "target eye" (i.e., treated eye). If both eyes of patients meet the inclusion criteria, the target eye will be medically determined by the investigator.  **Safety** **observation**  The investigational product rAAV2/8-hCYP4V2 Ophthalmic Injection is a gene replacement therapy product. In preliminary safety clinical study (ClinicalTrials No.: NCT04722107), enrollment, administration, and 3-month safety and efficacy observation have been completed in 3 subjects. During the observation period, no drug- or treatment-related serious adverse reactions occurred in any of the 3 subjects; meanwhile, 2 of the subjects showed significant improvements in visual acuity and MLMT score. It can be seen that the clinical dose of 5×10^8^ vg/uL has good safety and certain efficacy. In this clinical study, additional 9 subjects (12 subjects in total) are planned to be enrolled, and a total of 1 dose group, 7.5×10^10^ vg, is set. After one subject is enrolled first and no significant toxic and side effects are observed within 14 days after administration, the study in the second subject may be initiated. After the second subject completes administration and no significant toxic and side effects are observed within 14 days, the study in the third subject may be initiated; and so on. While conducting safety assessment, tear and blood samples are collected from subjects to detect DNA of rAAV2/8 virus and immune responses against the therapeutic vector.  **Preliminary Exploratory observation**  Clinical efficacy is preliminarily assessed by best-corrected visual acuity (BCVA, ETDRS chart), macular microperimetry, mfERG, color vision, dark-adapted contrast sensitivity, and MLMT. |
| Study Population  Inclusion Criteria  Subjects who meet all of the following inclusion criteria are considered eligible for participation in this study.  1) Age ≥ 18 years (inclusive) at the time of informed consent;  2) Patients with clinically confirmed Bietti's crystalline dystrophy (BCD);  3) Carrying two causative mutations in CYP4V2 gene confirmed by genetic testing;  4) Meet selection criteria for target eye;  5) The subject and his/her spouse agree to take effective contraceptive measures during the study and within 1 year after administration;  6) Voluntarily participate in this clinical study and have signed informed consent form.  Exclusion Criteria  Subjects meeting any of the following criteria will not be eligible to participate in this study.  1) The patient lacks sufficient viable retinal photoreceptor cells, has less than 1 disc area of retina photoreceptor cells or has a retinal thickness of less than 100 μm.  2) Active choroidal neovascularisation (CNV) lesion secondary to BCD in the target eye judged by the investigator; or other ocular disorders that would preclude surgery or interfere with interpretation of the study endpoints;  3) Medications within 3 months prior to screening that may affect study observation (e.g., Lucentis, Avastin, aflibercept, conbercept, triamcinolone acetonide, steroids, etc);  4) The target eye has received the following intraocular surgical treatments (PDT, vitrectomy, cataract surgery and retinal laser therapy required during the clinical study, periocular vascular bypass surgery, etc.);  5) Currently taking or may require systemic medications that can cause ocular toxicity, such as Psoralen, Risedronate, or Tamoxifen;  6) Hypersensitivity to any component of the investigational drug, or allergic constitution (e.g., allergy to two or more drugs or food);  7) Abnormal findings of physical examination, vital signs, laboratory tests (hematology, urinalysis, blood biochemistry, coagulation function, immunological examination, female blood pregnancy test), 12-lead ECG, chest X-ray judged by the investigator as clinically significant;  8) Having any past or present medical history that may affect the safety of the study or the metabolic process of the drug, especially the medical history of cardiovascular, hepatic, renal, endocrine, gastrointestinal, pulmonary, neurological, hematological, oncologic, immunological or metabolic disorders and others that are thought clinically significant by the investigator;  9) Participation in any clinical study of drug or medical device within 3 months prior to screening;  10) Patients with rAAV neutralizing antibody titer greater than 1:1000 detected by immunogenicity test;  11) Females who are pregnant or lactating;  12) Subjects who are not suitable for participation in this clinical study due to other reasons judged by the investigator. |
| **Sample Size:** 3 + 9 expected |
| **Study Procedure:**  Eligible subjects will be administered prednisone 3 days (Day -3) prior to dosing for 10 days at a dose of 1 mg/kg/day for the first 3 days. On the day of ZVS101e administration, vitrectomy is performed on the target eye according to the clinical practice, and 150 uL of the ZVS101e is injected into the subretinal space through a sterile injection needle for single use in strict accordance with the package insert of the drug. After surgery, routine treatment after vitrectomy is performed and prednisone is orally administered at 0.5 mg/kg/day for an additional 7 days without any treatment in the fellow eye. Patients have to lie supine for at least 14 hours following treatment (according to the clinical study results of Luxturna, 150 uL of the treatment vector was completely absorbed approximately 14 hours after local injection).  On D1, D2, D3, D7, D14, D28, D60, D90, D180, D270 and D365 after injection and at 15 months after the end of observation period, safety assessments were performed at corresponding time points, adverse events and concomitant medications are recorded for safety evaluation.  According to the blood collection points, biological samples are collected for relevant safety and immunogenicity evaluation.  Ocular functional tests (BCVA- ETDRS chart, macular microperimetry, mfERG, dark-adapted contrast sensitivity, and MLMT) and morphological test (color fundus photography, fundus autofluorescence (FAF) and OCT) are performed at visit points during the study to preliminarily evaluate the efficacy of the vector. |
| **Biological sample collection and testing:**  **Collection Points for rAAV Vector DNA Detection in Lacrimal Fluid:**  Tear is collected from subjects at pre-dose (baseline period), 3 h (D0), D1, D2, D3, D7, and D365 post-dose, and 15 months after the end of observation period to extract DNA. DNA samples are used to test the DNA concentration of rAAV vector and quantified using a validated real-time quantitative PCR (q-PCR).  **Collection Points for rAAV Vector DNA Detection in Peripheral Blood:**  Two mL of blood samples are collected from the upper limb vein of subjects and put into EDTA-anticoagulated blood collection tube (blood collection tube with purple cap) to separate leukocytes and extract DNA at each point at pre-dose (baseline period), 3 h (D0), D1, D7 and D365 post-dose, and 15 months after the end of observation period. DNA samples are used to test the DNA concentration of rAAV vector and quantified using a validated real-time quantitative PCR (q-PCR).  **Immunogenicity Blood Collection Points:**  Ten mL of blood samples are collected from the upper limb vein of subjects at each point at pre-dose (baseline period), D14, D28 and D365 post-dose, and 15 months after the end of observation period, and placed in BD 362761 peripheral blood mononuclear cell (PBMC) preparation tubes (CPT) to isolate PBMCs. PBMCs are used to test T cell immune response against rAAV vectors and T cell immune response against CYP4V2 protein, which are quantified using a validated ELISpot method.  Two mL of blood samples are collected from the upper limb vein of subjects and put into EDTA-anticoagulated blood collection tube (blood collection tube with purple cap) to obtain serum samples at each collection point at pre-dose (baseline period), D14, D28, D90 and D365 post-dose, and 15 months after the end of observation period. Plasma samples are used to detect rAAV vector neutralizing antibodies and quantified using a validated enzyme-linked immunosorbent assay (ELISA).  Two mL of blood samples are collected from the upper limb vein of subjects and put into blood collection tube containing coagulant (blood collection tube with orange-yellow cap) to obtain serum samples at each collection point at pre-dose (baseline period), D14, D28, D90 and D365 post-dose, and 15 months after the end of observation period Serum samples are used to detect humoral immune responses against CYP4V2 protein and quantified using a validated enzyme-linked immunosorbent assay (ELISA). |
| **Safety** **Evaluation:**  1) Adverse events: Ocular hypertension (excluding intraocular pressure slightly higher within postoperative 24 hours), endophthalmitis, vitreous hemorrhage, subretinal hemorrhage, retinal detachment (excluding within postoperative 14 hours), macular hole;  2) Ophthalmological examination:BCVA, intraocular pressure test (IOP, intraocular pressure in both eyes), slit-lamp examination, ophthalmoscopy, color fundus photography, FAF and OCT;  3) Vital signs, physical examination, chest X-ray and ECG;  4) General laboratory tests: Blood routine and urine routine, liver function and renal function tests, Serum virology tests, coagulation function test;  5) Vector shedding: Each subject was evaluated according to the concentration of rAAV vector DNA detected in tear and peripheral blood leukocytes.  6) Immunogenicity-: Each subject was evaluated based on cellular and humoral immune response against the therapeutic vector in the blood. |
| **Preliminary Exploratory Measures of Efficacy**  1. Functional assessments:  1) BCVA: Early Treatment Diabetic Retinopathy Study Visual Acuity Scale (ETDRS Chart) is used to examine visual acuity at pre-dose (baseline period), D1, D2, D3, D14, D28, D60, D90, D180, D270 and D365 post-dose, and 15 months after the end of observation period;  2) Color vision test: Atlas for colorblindness is used to assess color vision at pre-dose (baseline period), D28, D60, D180 and D365 post-dose, and 15 months after the end of observation period;  3) Dark-adapted contrast sensitivity test: This test is used to compare the changes in scotopic contrast sensitivity at pre-dose (baseline period), D28, D60, D180 and D365 post-dose, and 15 months after the end of observation period;  4) Macular microperimetry and mfERG: This examination is used to compare the changes in macular retinal function and macular microperimetry at pre-dose (baseline period), D28, D60, D180 and D365 post-dose, and 15 months after the end of observation period;  2. Behavioral assessments:  MLMT is used to test the behavioral changes of subjects at pre-dose (baseline period), D28, D60, D180 and D365 post-dose, and 15 months after the end of observation period;  3. Morphological assessments:  Color fundus photography, fundus autofluorescence (FAF) and OCT are used to examine changes of retinal morphology and retinal cells in each layer at pre-dose (baseline period), D1, D2, D3, D14, D28, D60, D90, D180, D270 and D365 post-dose, and 15 months after the end of observation period. |

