# Table 1. Study Flow Chart

|  | Screening/Baseline period | Observation period | | | | | | | | | | | | | Follow-up period |
| --- | --- | --- | --- | --- | --- | --- | --- | --- | --- | --- | --- | --- | --- | --- | --- |
| Time of visit | V1 | V2 | V3 | V4 | V5 | V6 | V7 | V8 | V9 | V10 | V11 | V12 | V13 | V14 | V15 |
|  | B1  (1w pre-op) | D-3 | D0 | D1 | D2 | D3 | D7 | D14  ±2d | D28  ±5d | D60  ±5d | D90  ±5d | 180  ±30d | D270  ±30d | D365^8^  ±30d | 15 months ± 30 d after the end of observation period |
| Sign informed consent form | X |  |  |  |  |  |  |  |  |  |  |  |  |  |  |
| Demographic data | X |  |  |  |  |  |  |  |  |  |  |  |  |  |  |
| Medical and treatment history | X |  |  |  |  |  |  |  |  |  |  |  |  |  |  |
| Verification of inclusion/exclusion criteria | X |  |  |  |  |  |  |  |  |  |  |  |  |  |  |
| Physical examination | X |  |  | X |  |  |  |  | X |  | X |  |  | X | X |
| Serum pregnancy test^1^ | X |  |  |  |  |  |  |  |  |  |  |  |  |  |  |
| Start of prednisone administration |  | X |  |  |  |  |  |  |  |  |  |  |  |  |  |
| Surgical administration |  |  | X |  |  |  |  |  |  |  |  |  |  |  |  |
| End of prednisone administration |  |  |  |  |  |  | X |  |  |  |  |  |  |  |  |
| Vital signs ^2^ | X |  | X | X | X | X | X | X | X | X | X | X | X | X | X |
| ECG | X |  | X | X |  |  | X | X | X | X | X | X | X | X | X |
| Chest X-ray | X |  |  |  |  |  |  |  | X |  |  |  |  | X | X |
| Blood routine^3^ | X |  |  | X |  |  | X | X | X | X |  | X |  | X | X |
| Urine routine^3^ | X |  |  | X |  |  | X | X | X | X |  | X |  | X | X |
| Blood chemistry^3^ | X |  |  | X |  |  | X | X | X | X |  | X |  | X | X |
| Serum virology tests^3^ | X |  |  | X |  |  | X |  | X |  |  |  |  | X | X |
| Coagulation function test^3^ | X |  |  | X |  |  | X |  | X |  |  |  |  | X | X |
| Collection of lacrimal fluid | X |  | X | X | X | X | X |  |  |  |  |  |  | X | X |
| Collection of peripheral blood leukocytes | X |  | X | X |  |  | X |  |  |  |  |  |  | X | X |
| Collection of peripheral blood mononuclear cells^4^ | X |  |  |  |  |  |  | X | X |  |  |  |  | X | X |
| rAAV vector neutralizing antibodies in peripheral blood plasma^5^ | X |  |  |  |  |  |  | X | X |  | X |  |  | X | X |
| CYP4V2 protein antibodies in peripheral blood serum^5^ | X |  |  |  |  |  |  | X | X |  | X |  |  | X | X |
| General ophthalmological examination ^6^ | X |  |  | X | X | X |  | X | X | X | X | X | X | X | X |

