### 6.1.2 Observation period

V2 (D-3), the following items should be completed:

1) Prednisone is administered orally at a dose of 1 mg/kg/day;

2) Adverse events, concomitant medications, treatments

V3 (D0), the following items should be completed:

1) Vital signs (within 1 h pre-dose and 1 h ± 15 min, 3 h ± 30 min post-dose)

2) Prednisone is administered orally at a dose of 1 mg/kg/day

3) Subretinal injection

4) ECG (3 h ± 30 min post-dose)

5) Biological sample collection and testing (3 h ± 30 min post-dose): Collection of tear and peripheral blood leukocytes

6) Adverse events, concomitant medications, treatments

V4 (D1), the following items should be completed:

1) Physical examination

2) Vital signs

3) ECG

4) Laboratory tests: Blood routine/urine routine/blood chemistry; Serum virology tests; coagulation function;

5) Biological sample collection and testing: Collection of tear and peripheral blood leukocytes

6) General ophthalmological examination: Including intraocular pressure, slit-lamp examination and ophthalmoscopy

7) BCVA assessment

8) Color fundus photography and FAF

9) OCT (optical coherence tomography)

10) Prednisone is administered orally at a dose of 0.5mg/kg/day

11) Adverse events, concomitant medications, treatments

V5 (D2), the following items should be completed:

1) Vital signs

2) Biological sample collection: Collection of lacrimal fluid

3) General ophthalmological examination: Including intraocular pressure, slit-lamp examination and ophthalmoscopy

4) BCVA (best-corrected visual acuity) assessment

5) Color fundus photography and FAF

6) OCT (optical coherence tomography)

7) Prednisone is administered orally at a dose of 0.5 mg/kg/day

8) Adverse events, concomitant medications, treatments

V6 (D3), the following items should be completed:

1) Vital signs

2) Biological sample collection and testing: Collection of tear

3) General ophthalmological examination: Including intraocular pressure, slit-lamp examination and ophthalmoscopy

4) BCVA (best-corrected visual acuity) assessment

5) Color fundus photography and FAF

6) OCT (optical coherence tomography)

7) Prednisone is administered orally at a dose of 0.5mg/kg/day

8) Adverse events, concomitant medications, treatments

V7 (D7), the following items should be completed:

1) Prednisone is administered orally at a dose of 0.5 mg/kg/day, last dose

2) Vital signs

3) ECG

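### The prednisone course is 10 days in the synopsis but counts to 11 days in section 6.1.2, and the two do not agree on the day of surgery

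*Protocol*

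**What the plan says.** Three places in the protocol describe the prednisone course.

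- **Protocol Synopsis, Study Procedure.** Eligible subjects are "administered prednisone 3 days (Day -3) prior to dosing for 10 days at a dose of 1 mg/kg/day for the first 3 days". After the operation, "prednisone is orally administered at 0.5 mg/kg/day for an additional 7 days". No dose is named for the day of surgery itself.
- **Section 6.1.2, Observation period.** At V2 (D-3): "Prednisone is administered orally at a dose of 1 mg/kg/day". At V3 (D0), the day of the subretinal injection: "2) Prednisone is administered orally at a dose of 1 mg/kg/day". At V4 (D1): "10) Prednisone is administered orally at a dose of 0.5mg/kg/day". The same lower dose is listed at V5 (D2) and V6 (D3). At V7 (D7): "Prednisone is administered orally at a dose of 0.5 mg/kg/day, last dose".
- **Table 1, Study Flow Chart.** The row "Start of prednisone administration" is marked at V2 (D-3) and the row "End of prednisone administration" at V7 (D7). The table gives no doses.

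Section 5.1.2 and the concomitant-therapy lists in section 5.2 contain no prednisone regimen, and nothing in the protocol says which of the three places prevails.

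**The concern.** The synopsis fixes a course of 10 days with 3 at the higher dose. The visit schedule, read as daily dosing, gives 11 days with 4 at the higher dose. Staff working from one place will treat a subject differently from staff working from the other, and a monitor holding the other text could record a deviation either way.

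The protocol itself treats steroids as relevant to its readouts. Exclusion criterion 3 lists them among drugs that can affect study observation, and sections 3.2 and 5.2.3 describe vector-related inflammation as controllable with hormone or corticosteroid treatment. Ocular hypertension and immunogenicity are safety measures. The disputed days also lie inside the 14-day window that must pass without significant toxicity before the next subject starts. With 12 subjects in total and no control arm, variation in steroid cover around the injection would be hard to separate from the effect of the vector.

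**Working it through.** **Inputs.** Synopsis: start D-3, 10 days in all, 3 at 1 mg/kg/day, 7 at 0.5 mg/kg/day. Section 6.1.2: 1 mg/kg/day at D-3 and D0; 0.5 mg/kg/day at D1, D2, D3 and D7, the last marked as the final dose. Section 6.1.2 lists visit days only, so D-2, D-1 and D4 to D6 are filled in because the doses are stated per day.

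**The synopsis's own figure.** 3 + 7 = 10 days, so it is internally consistent. Cumulative dose: 3 × 1 + 7 × 0.5 = 6.5 mg/kg.

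**Section 6.1.2.** D-3, D-2, D-1, D0 = 4 days at 1 mg/kg; D1 to D7 = 7 days at 0.5 mg/kg. Total 4 + 7 = 11 days. Cumulative dose: 4 × 1 + 7 × 0.5 = 7.5 mg/kg.

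**Can the synopsis be read to match?** Counting from D-3, the first three days are D-3, D-2 and D-1, which leaves two readings.

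| | Days | Days at 1 mg/kg | D0 dose | Last dose | Cumulative |
|---|---|---|---|---|---|
| Synopsis, no gap | 10 | 3 | 0.5 mg/kg | D6 | 6.5 mg/kg |
| Synopsis, the seven days starting D1 | 10 | 3 | none | D7 | 6.5 mg/kg |
| Section 6.1.2 | 11 | 4 | 1 mg/kg | D7 | 7.5 mg/kg |

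The first reading disagrees with section 6.1.2 on both the D0 dose and the last day. The second agrees on the last day but leaves D0 undosed.

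As a cross-check, ten consecutive days ending on D7 would have to begin on D-2, whereas all three places begin on D-3. Ten is the elapsed difference 7 − (−3); the inclusive count of dosing days is 11.

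**Size.** 7.5 / 6.5 = 1.154, about 15% more. For an assumed body weight of 60 kg: 6.5 × 60 = 390 mg against 7.5 × 60 = 450 mg.

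**The case against.** The best defence is that this is a loose count of a single day. All three places start on D-3, Table 1 and section 6.1.2 both end on D7, and the synopsis's seven postoperative days fit D1 to D7. Taken as elapsed time, every synopsis figure reproduces: D-3 to D0 is 3, D0 to D7 is 7, D-3 to D7 is 10. This may well explain how the discrepancy arose, but it does not remove it. The synopsis assigns the higher dose to the first three days of a daily course, and D0 is the fourth.

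Several limiting points do stand:

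- The synopsis gives no dose for D0, so the conflict there is inferred from its day count. The total of 11 days in section 6.1.2 is likewise a count and is not printed there.
- The primary objective concerns the safety of the vector injection, and prednisone is not part of the investigational drug. The steroid matters as background treatment that can influence the safety readouts.
- The last dose moves by one day at most (D6 or D7), while the D14 visit has a window of ±2 days, so the effect on the timing of that immunogenicity sample is small.
- Nothing shows that one day of steroid would change an inflammation, pressure or immune result, or move a subject out of the Per-Protocol Set.
- Sections 5.2.1, 5.2.5 and 6.2.8 already require dose and timing of all other medication to be recorded, so actual exposure should be recoverable for subjects treated under this protocol.

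**Conclusion.** The concern holds. The synopsis and section 6.1.2 give prednisone courses that cannot both be followed: 10 days against 11, 3 days at 1 mg/kg against 4, and on the day of surgery either 0.5 mg/kg or no dose against 1 mg/kg. The difference amounts to one dosing day and 1 mg/kg of cumulative dose. Table 1 supports section 6.1.2 on the start and end days but is silent on dose, so it does not settle D0.

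The totals assume uninterrupted daily dosing between the listed visits. The D0 and D7 instructions in section 6.1.2 are explicit and do not depend on that assumption. The consequence is inconsistent treatment delivery and avoidable deviations in a small safety study. The planned sample size and analyses are unaffected. It should be corrected.

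**What to change.** Reconcile the synopsis, Table 1 and section 6.1.2 into one day-by-day prednisone schedule that states the dose on D0, the total number of dosing days and the day of the last dose, and use it unchanged in all three places. The sponsor and investigator must decide which schedule is meant; this review takes no position on that.

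Tabulate the prednisone each subject actually received, by day, from the concomitant-medication record. Because the 12 subjects include 3 from the preliminary study, state also what those 3 received. That study's protocol is not at hand, so it cannot be assumed that they followed either schedule.

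The cost is a protocol text correction and one listing from data already required. The design, sample size and analysis do not change.
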